**Background of Research**

*Prevalence and impacts of dysmenorrhea****.*** Primary dysmenorrhea is a debilitating condition that affects nearly half of all menstruating women worldwide.^1^ A cross-sectional survey performed in 2013 in Hong Kong (HK) found that out of 240 18–25-year-old female university students, the prevalence of dysmenorrhea was 80%.^2^ Primary dysmenorrhea has been linked to regular educational absenteeism,^3^ and the class attendance rate among women has been reported to decrease by 29%–50% during menstruation.^4^ Recurrent absenteeism has negative impacts on young women, decreasing the total contact time for learning, which may affect the quality of the educations they receive.^3^ Studies that have examined the impacts of primary dysmenorrhea on daily life have reported that adolescent women with primary dysmenorrhea experience the reduced ability to concentrate, educational disruptions,^2^ and lower academic performance.^5^ The effects of primary dysmenorrhea-associated pain extend beyond individual women to society, resulting in regular work absenteeism.^5^

*Pathophysiology of primary dysmenorrhea.* The pathogenesis of primary dysmenorrhea has been linked to abnormally elevated prostaglandin secretion.^1, 6^ Abnormally high prostaglandin levels cause frequent and dysrhythmic uterine contractions, resulting in ischemia and hypoxia, which are considered to be major contributors to primary dysmenorrhea-associated pain.^1, 7^ Aetiological studies have reported that prostaglandin production is regulated by progesterone with prostaglandins and progesterone displaying an inverse relationship.^1, 6, 8^

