***Pilot trial***: We conducted a pilot trial to examine the effects of HIAT on plasma biomarkers that have been implicated in the pathophysiology of primary dysmenorrhea. The pilot trial findings indicated a trend towards increased progesterone levels (***d*** = 0.36) and decreased levels of prostaglandin F2 alpha (PGF2α) metabolites (***d*** = 0.35) in the HIAT group compared with those in the control group, which suggested that aerobic exercise may affect primary dysmenorrhea pain through effects on these mediators.^8, 13^

Because our research has supported the beneficial effects of HIAT, and a recent pilot study suggested a link between HIAT and progesterone and prostaglandin levels, the proposed randomised, controlled cross-over trial will test the following three hypotheses: (1) HIAT for 12 weeks will lead to significant reductions in pain intensity and absenteeism and improve academic performance compared to baseline levels; (2) pain improvements will be mediated by increased progesterone levels, resulting in decreased PGF2α levels; (3) HIAT will display superior cost-effectiveness compared with usual care (Wait-list control [WLC]) for primary dysmenorrhea treatment.

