**Statistical tests and anticipated results**

*Missing data and data preparation*. We will implement strategies, such as the digital diary, follow-up phone-call reminders, and providing routine encouragement to continue exercise, to minimise missing data. Missing values will be replaced with group means. All statistical analyses will be performed on an intention-to-treat basis, using SPSS (version 24).

***Hypothesis 1.*** The two phases that each participant completes during the course of a cross-over trial are typically referred to as the two study periods.^49^ First, a preliminary test will be carried to rule out carryover effects and to test our study for validity.^50^ This will be performed by estimating the sum of the values measured during the two treatment periods for each participant and compared across the groups by using an independent samples *t*-test.^49^ Second, the within-participant differences in outcome variables between the study periods will be calculated using a two-sided Student’s unpaired *t*-test.^49, 50^ Treatment effects will be evaluated using an ANOVA with a mixed-effects model considering the longitudinal repeated measures, including the effects of time (T1, T2, and T3) within each study group and the interaction between time and intervention. Post hoc analysis using the Bonferroni correction will be performed. Hypothesis 1 will be supported if significant reductions in pain intensity and university absenteeism and a significant improvement in academic performance are reported following 12 weeks of HIAT compared with baseline measurements.

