***Hypothesis 2.*** The mediation effects of increased progesterone levels on pain will be assessed using the Sobel test.^51^ A four-step model using linear regression will be tested. In Step 1, the regression coefficient between prostaglandin levels and pain (Path C) will be estimated. In Step 2, the regression coefficient between progesterone and prostaglandin levels (Path A) will be estimated. In Step 3, the regression coefficient between pain and prostaglandin levels, along with the mediator, progesterone levels (Path B), will be evaluated. Step 4: the Sobel test will be used to estimate the standard error of Path AB using the formula B^2^SA^2^ + A^2^SB^2^, where A and B are the regression coefficients of Paths A and B, respectively, and SA and SB are the standard errors of Paths A and B, respectively.^51^ The online Sobel test calculator (<http://quantpsy.org/sobel/sobel.htm>) will be used. Hypothesis 2 will be supported if the Sobel test indicates a significant (p < 0.05) mediation effect.

***Hypothesis 3***. The unadjusted mean costs and cost differences between HIAT and the usual care groups for total and disaggregated costs (intervention costs, healthcare utilisation costs, including healthcare services and medications utilised, and absenteeism costs) will be calculated.^48^ The seemingly unrelated regression (SUR) analyses will be used to estimate the total cost differences (ΔC) and effect differences (ΔE). The SUR analyses will be performed by adjusting for baseline demographic and health characteristics (such as pain intensity and menstrual-cycle length or the number of bleeding days) between groups.^48, 52^ The advantage of SUR is that two regression equations, one for ΔC and one for ΔE, are modelled simultaneously allowing possible correlations between cost and outcome differences to be accounted for.^48, 53^

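### The Hypothesis 2 decision rule accepts any significant Sobel test and requires no direction, so a reversed progesterone mechanism meets it as easily as the hypothesised one

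*Protocol*

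**What the plan says.** The hypotheses at the end of the Background of Research section give Hypothesis 2 as: "pain improvements will be mediated by increased progesterone levels, resulting in decreased PGF2α levels". The same direction is repeated under Scientific premises for the study hypotheses. The Background supplies the biological premise: "prostaglandins and progesterone displaying an inverse relationship".

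Under Statistical tests and anticipated results, the Hypothesis 2 paragraph opens: "The mediation effects of increased progesterone levels on pain will be assessed using the Sobel test". It then lists these steps:
- Step 1 relates prostaglandin to pain (Path C).
- Step 2: "the regression coefficient between progesterone and prostaglandin levels (Path A) will be estimated".
- Step 3: "the regression coefficient between pain and prostaglandin levels, along with the mediator, progesterone levels (Path B), will be evaluated".
- Step 4 takes the "standard error of Path AB using the formula B^2^SA^2^ + A^2^SB^2".

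The paragraph closes with the rule: "Hypothesis 2 will be supported if the Sobel test indicates a significant (p < 0.05) mediation effect".

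The rule for Hypothesis 1 in the same section is directional: "Hypothesis 1 will be supported if significant reductions in pain intensity and university absenteeism and a significant improvement in academic performance". The rule for Hypothesis 3 asks for savings and lower healthcare use, so it is directional too.

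**The concern.** The rule for declaring support is weaker than the hypothesis. The hypothesis fixes three directions and the rule fixes none. Data in which higher progesterone goes with higher PGF2α and with more pain would satisfy the rule as written, although they contradict the mechanism.

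Progesterone and PGF2α are named as the trial's primary mediators, and this sentence governs its only mechanistic claim. A report that followed the rule literally could state that increased progesterone mediates pain relief when the estimates point the other way.

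**Working it through.** **1. What the statistic can see.** Inputs: A is the progesterone–prostaglandin coefficient (Step 2). B is the coefficient of progesterone for pain with prostaglandin in the model (Step 3). SA and SB are their standard errors. The printed expression is the variance of AB, so I use its square root:

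z = AB / √(B²SA² + A²SB²)

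The denominator contains A and B only as squares. Changing the sign of either coefficient can change the sign of z but not its size, so the two-sided p-value is unchanged.

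**2. Worked values.** The protocol gives no path sizes. Assume |A| = |B| = 0.4 and SA = SB = 0.1. The variance is 0.16 × 0.01 + 0.16 × 0.01 = 0.0032, its square root is 0.0566, and 0.16 / 0.0566 = 2.83.

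| A | B | z | two-sided p |
|---|---|---|---|
| −0.4 | −0.4 | +2.83 | 0.0047 |
| +0.4 | +0.4 | +2.83 | 0.0047 |
| −0.4 | +0.4 | −2.83 | 0.0047 |
| +0.4 | −0.4 | −2.83 | 0.0047 |

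The first two rows share the sign of z as well as the p-value. A one-sided test, or a check on the sign of AB, therefore cannot tell a pattern from its complete reversal.

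**3. How often the rule is met.** The two regressions were simulated with prostaglandin as predictor, progesterone as mediator and pain as outcome. Sample sizes were n = 130 (enrolled) and n = 91 (130 × 0.7, after the planned 30% attrition). Path sizes are assumptions.

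| Assumed size of each path | n = 91 | n = 130 |
|---|---|---|
| 0.3, range over the four sign patterns | 44–47% | 72–74% |
| 0.4, range over the four sign patterns | 83–84% | 96–97% |
| 0 (both null) | under 0.1% | under 0.1% |

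Separate simulations with paths of 0.3 and other modelling assumptions gave 42–52% at n = 91 and 70–81% at n = 130. The level moves with the assumptions. In every version the rate was about the same for all four sign patterns.

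**4. Which signs the hypothesis implies.** The hypothesis runs HIAT → progesterone → PGF2α → pain. If progesterone affects pain only through PGF2α, its coefficient for pain given PGF2α is zero. Path B as written is exactly that adjusted coefficient, so B ≈ 0 and AB ≈ 0 under the stated chain. Simulating this chain with links of −0.3 and +0.3 gave a significant Sobel test in 1.4% of runs at n = 91 and 1.7% at n = 130. With links of 0.4 it was 2.3% and 3.6%. Only about half of those significant runs had both A and B negative. The hypothesised direction therefore cannot be written as A < 0 and B < 0 in the present model.

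**5. The same gap in a model that includes treatment.** Along the stated chain the links should be positive (HIAT raises progesterone), negative (progesterone lowers PGF2α) and positive (PGF2α raises pain), giving a negative product. Three links have 2³ = 8 sign patterns, and four of them give a negative product. Only one of those four is the hypothesis. The links must be checked one by one in that model too.

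**The case against.** The strongest reply is that direction is already stated where the hypothesis is defined and again in the opening sentence of the analysis paragraph, so the mediation effect in the closing rule means that effect. Paths A, B and C are also estimated separately, so the analysts would see the signs. This is a fair account of intent. It does not change the criterion: the opening phrase describes an aim, none of the four steps tests whether progesterone increased, and the closing sentence makes p < 0.05 sufficient. Nor is this detail left to an SAP, because the protocol itself fixes the rule.

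A second reply is that the larger fault is the model. HIAT appears in no step, and prostaglandin is the predictor with progesterone as mediator. That is correct and it limits the remedy: a sign condition added to the present regressions would not make a significant result evidence for Hypothesis 2. Re-specifying the model would not remove the need for a sign condition either (step 5 of the working).

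Three stronger readings are tempting but not supported:
- A reader might infer that A < 0 with B < 0 is the one pattern that fits, so that one added sentence suffices with no loss of power. Step 4 shows otherwise: that pattern needs a direct effect of progesterone on pain, which the protocol does not state.
- A reader might take 45% or 73% as the trial's chance of a false conclusion. These are rejection rates given assumed non-zero paths. With both paths null the rule was met in under 0.1% of runs.
- A reader might infer that reversal is likely. The protocol's own evidence points the other way: the inverse relation in the Background, and pilot trends of higher progesterone (d = 0.36) and lower PGF2α metabolites (d = 0.35).

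**Conclusion.** The point holds as a fault in the stated rule. A significant Sobel test with reversed paths meets the criterion for Hypothesis 2 exactly as readily as one with any other signs, and the sign of AB alone does not separate them. This follows from the formula and needs no assumption.

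The size does need assumptions. About 45% at n = 91 and 73% at n = 130 are illustrations for paths of 0.3, a value the protocol does not give. What they show is that the rate does not depend on sign. They do not show how probable a reversal is.

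The rule should be changed before analysis, because it governs the trial's mechanistic conclusion and the change is cheap.

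**What to change.** Replace the closing sentence of the Hypothesis 2 paragraph with a rule of this kind: Hypothesis 2 is supported only if the indirect effect along HIAT → progesterone → PGF2α → pain is significant, and the estimated links have the hypothesised signs (HIAT raises progesterone; higher progesterone goes with lower PGF2α; higher PGF2α goes with more pain). Report the indirect effect with its sign and confidence interval, together with each link. Report a significant result with any other sign pattern as not supporting Hypothesis 2.

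State the signs on these causal links and not on A and B as now defined. The regressions must then include randomised treatment and follow that order, which is a small re-specification beyond the reworded sentence. It uses only allocation, the salivary measures and the pain score, all of which the protocol already plans to collect. The cost is a short protocol amendment. The sign condition should cost little power when the mechanism is as hypothesised, but power for the re-specified indirect effect has not been calculated here and would need assumed path sizes.

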***Intervention.*** The exercise intervention will last for 24 weeks (12 weeks for the HIAT group and 12 weeks for the WLC group) at PolyU. Supervised treadmill (Zebris FDM-T) training at PolyU will begin on the first day of the second menstrual period (baseline assessments will be completed during the first menstrual period). Exercise sessions at PolyU will be instructed and supervised by a registered physiotherapist (RPg student). Using this supervisory method, the participant-to-research person ratio will be 1:1. The rationale for providing supervised sessions is to increase adherence to study interventions because, in our previous RCT^9^, adherence was higher for supervised sessions than for unsupervised home exercise sessions. MHR will be calculated using the conventional age-predicted formula (220 – age). To achieve the target HR, the speed of the treadmill will be gradually increased, based on the participants’ HR, which will be displayed on the treadmill, and the rating of perceived exertion (RPE). Because the current proposed study does not involve graded, incremental exercise, graded-exercise testing (such as VO_2max_ evaluation) will not be performed.

*HIAT.* Women will perform treadmill-based aerobic exercise for three days a week, at 70%–85% of MHR for 30 minutes and perceived exertion of 14–16, based on the Borg RPE scale. This range^39^ is considered to represent HIAT. Aerobic training will be preceded by warm-up exercises for 10 minutes and followed by cool-down exercises for 10 minutes, at a perceived exertion of 11.0 (Borg RPE). These exercise parameters are based on our previous studies^9,10^ and the American College of Sports Medicine guidelines.^40^

*WLC*. Women in the WLC group will be instructed to continue with their usual activities and manage their pain as normal (i.e., with analgesics).

**Outcome measures: Primary outcomes:** *Pain intensity.* Average pain intensity during the last 24 hours during menstruation will be assessed using the 0–10 NRS,^41^ with 0 representing ‘No pain’ and 10 representing ‘Worst imaginable pain’.

*Absenteeism from university*: Access to a prospective electronic diary will be provided for each participant to record university absenteeism. Electronic diaries are reported as highly acceptable and feasible to use.^44^ Significantly increased compliance and accuracy have been reported with e-diary recording compared with traditional paper diaries.^44^

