*Economic evaluation*. We will analyse the results of HIAT versus WLC over a 12-week, within-trial period (i.e., at T2).^28^ The cost-effectiveness for the entire 28-week time horizon will also be explored through T3 data observed in the HIAT arm and extrapolation of WLC data.^28^ The primary analysis will be conducted from a societal perspective (short-term direct costs, intervention costs, costs unrelated to the intervention [healthcare services and medication costs] and indirect costs, such as absence from work and impact on productivity due to primary dysmenorrhea).^48^ The secondary analysis will be conducted from a healthcare perspective (direct costs, including intervention costs and costs of other care, *excluding* absenteeism costs).^48^ Cost and absenteeism data that are collected at baseline (i.e., previous three menstrual cycles) will be used as predictors of future costs in the analysis. The EQ-5D-3L will be used to determine the QoL for the HIAT and WLC groups. The cost per participant will be calculated by multiplying unit costs identified from the HK government standardised national price list and resource quantities.^28^

An electronic diary (<https://forms.gle/gvoLHAoDqySQFr4GA>) will be used to record cost expenditures and work absenteeism. All participants will be provided with access to the cost diary, post-randomisation. Participants with limited access to the internet will be provided with printed hard copies of the cost and absenteeism diary, along with stamped and addressed return envelopes. Participants will be instructed to complete the diary during the week of menstruation each month. The research team members will be able to access the electronic diary to obtain a summary of the completed items for all study participants. The student assistant will contact participants by telephone for incomplete entries, to acquire additional details, or for failure to complete the diary.

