**Qualitative study (semi-structured focus groups):** The qualitative study will provide insight into the participants’ experiences during and attitudes towards the study intervention. During focus group discussions, attempts will be made to identify the subjective experiences with participation in HIAT and participants’ perceived improvements in menstrual pain, university attendance, and academic performance. For this component of the research, a computer-generated randomisation schedule will be generated and utilised to identify 70 participants (from the 130 participants included in the RCT), to participate in the focus groups. Ethics approval and written informed consent will be obtained before enrolment. A total of seven focus groups will be conducted at 32 weeks post-randomisation. Each group will consist of a random sample of 8-10 participants and will last between 30 and 45 minutes. Focus groups will be conducted in private rooms at PolyU. If the coronavirus disease 2019 pandemic continues, face-to-face seminars will be replaced with virtual meetings (Zoom) to allow appropriate social distancing. Two researchers, a moderator (PI) and a co-moderator (RPg student), will conduct the focus groups, and a third research team member will take notes. The interviews will be recorded using a digital voice recorder, in addition to taking notes. Semi-structured discussion guides will be used.

***Treatment fidelity and missed sessions.*** To optimise adherence to exercise sessions at PolyU, a student assistant will contact any participant who has missed an exercise session and attempt to re-schedule that session. Following the baseline assessment, all participants will be provided with information regarding how to access and complete the electronic diaries.

***Retention plan.*** To maximise retention we: (1) will obtain the contact information of participants and any friends and relatives who may know their whereabouts, and obtaining permission to follow-up the listed contact persons; (2) include appointments for data collection in the study schedule; (3) schedule supervised exercise at convenient times; and (4) offer a remuneration of HK$ 200 to cover the costs incurred during study participation.

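### The societal cost total has no place for participants' time, and no clear place for their travel, for up to 36 HIAT sessions; leaving these out would favour HIAT at T2

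*Protocol*

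**What the plan says.** In the protocol's Economic evaluation section the primary perspective and its direct components are stated as "The primary analysis will be conducted from a societal perspective (short-term direct costs, intervention costs, costs unrelated to the intervention [healthcare services and medication costs", to which are added "indirect costs, such as absence from work and impact on productivity due to primary dysmenorrhea". The secondary, healthcare perspective keeps intervention and other care costs and drops absenteeism.

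Under Statistical tests and anticipated results, Hypothesis 3, the quantities to be calculated are "total and disaggregated costs (intervention costs, healthcare utilisation costs, including healthcare services and medications utilised, and absenteeism costs". Later in that section the healthcare analysis is again obtained by taking absenteeism out.

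Costs are captured in an electronic diary that "will be used to record cost expenditures and work absenteeism", and "Participants will be instructed to complete the diary during the week of menstruation each month". On the intervention, the plan says: "Women will perform treadmill-based aerobic exercise for three days a week". Sessions are supervised on campus at PolyU. WLC women carry on with their usual activities. Hypothesis 3 counts as supported only if HIAT saves direct and indirect costs at T2 and healthcare use is also lower.

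**The concern.** A societal analysis should count what the programme costs the women who take part as well as what it costs the provider. Here, time lost to dysmenorrhoea is a cost, but time given to the treatment appears under no heading. Up to T2 that time is spent in one arm only, so leaving it out does not cancel between arms. It lowers the cost difference and moves the ICER and the acceptability curve towards HIAT, whatever the programme's real effect. Because the Hypothesis 3 rule asks for cost savings, a small true excess cost could be reported as a saving.

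**Working it through.** The protocol gives no cost figure, so there is nothing to reproduce. The check compares the component lists and then does simple arithmetic.

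**1. Component lists**

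| Component | Economic evaluation section | Hypothesis 3 total |
|---|---|---|
| Short-term direct costs | named, undefined | not named |
| Intervention costs | named, undefined | named |
| Healthcare and medication | named | named |
| Absence | named (work) | named |
| Productivity loss due to dysmenorrhoea | named | not named |
| Participant time in sessions | not named | not named |
| Participant travel to sessions | not named | not named |

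In both sections absenteeism is the only item that separates the societal from the healthcare analysis. Participant time and travel are therefore either in neither total, or they sit inside intervention costs and stay in the healthcare total, where they do not belong. Session time fits badly under the indirect costs, whose examples relate to the disease. It is also neither an expenditure nor a work absence, the two things the diary records.

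**2. Hours per fully adherent HIAT woman before T2**

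- Sessions: 3 per week x 12 weeks = 36 (Intervention; Procedure).
- Minutes per session: 10 warm-up + 30 exercise + 10 cool-down = 50 (Intervention).
- Time: 36 x 50 / 60 = 30 h. In WLC: 0 h.

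**3. Travel (assumed; the documents give no figure)**

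Hours = 36 x (50 + R) / 60, where R is the round trip in minutes.

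- R = 30: 36 x 80 / 60 = 48 h
- R = 60: 36 x 110 / 60 = 66 h
- R = 90: 36 x 140 / 60 = 84 h

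**4. Money (assumed HK$40 to 100 per hour, fares HK$0 to 40 per session)**

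- No travel: 30 x 40 = HK$1,200 to 30 x 100 = HK$3,000.
- R = 60: 66 x 40 = HK$2,640 to 66 x 100 = HK$6,600.
- Fares: 36 x 0 = HK$0 to 36 x 40 = HK$1,440.
- Highest total with R up to 60: 6,600 + 1,440 = HK$8,040.
- Lowest total, with time valued at zero and no travel: HK$0.

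**5. Effect on the comparison**

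Let A be sessions attended, F the fare and V the hourly value of time. The omitted amount is B = the HIAT-arm mean of A x [F + V x (50 + R) / 60]. The corrected cost difference is the planned difference plus B, because the WLC term is zero up to T2. If the planned difference lies between -B and 0, the plan would report a saving where the fuller societal account shows none.

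A averages less than 36. As an illustration only, if 30% of women (the attrition allowance in the sample size section) attended nothing and the rest attended every session, mean time would be 0.70 x 30 = 21 h.

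**6. Whether the plan would reveal it**

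One planned sensitivity analysis restricts to completers and the other drops cost outliers. Neither changes which costs are counted. The exploratory 28-week analysis extrapolates WLC data, so the sessions WLC women attend after cross-over would not evidently restore the balance.

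**The case against.** The best reply is that silence is not exclusion. Intervention costs and short-term direct costs are undefined, the indirect costs are introduced by examples, and the diary takes expenditures, which could include fares. Item-level costing often belongs in an analysis plan, and none is shown here. This stands for travel, so the point on travel is only that the plan is unclear. It carries less weight for own time, which has no evident home under any heading. Nor does it answer the fact that the two perspectives differ by absenteeism alone.

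A reader might infer that travel cannot be captured because the diary is filled in during the menstrual week. The protocol states when the diary is completed, not the period it covers; a monthly entry could look back over the month. Session time could also be recovered from attendance, since supervision is one to one and missed sessions are followed up.

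A reader might also infer that the omitted time outweighs any absenteeism saved. If HIAT saved one 8-hour day in each of three cycles (24 h), 30 to 66 h would be 30/24 = 1.25 to 66/24 = 2.75 times that saving. The saving, the travel and the equal valuation of hours are all assumptions. Sessions are to be scheduled at convenient times and may displace leisure, so valuing them at the absenteeism rate is open to dispute. In that same example, about 30 h of one-to-one supervision, presumably already an intervention cost, would outweigh the 24 h at a common hourly value. The example therefore does not show that participant time reverses a conclusion.

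The cost is not positive in every HIAT woman: the analysis is by intention to treat, and a woman who attends nothing adds nothing. The plan's intention to "offer a remuneration of HK$ 200 to cover the costs incurred during study participation" is a retention measure not tied to one arm, and it says nothing about how session costs are treated. Lower healthcare use, the other half of the Hypothesis 3 rule, is unaffected.

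**Conclusion.** The concern holds in a limited form. The protocol declares a societal perspective but does not provide for participants' own time in HIAT sessions, and does not clearly provide for their travel. Up to T2 the burden falls on HIAT alone, at up to 30 h per fully adherent woman before travel. If it is left out, the societal cost difference moves towards HIAT on the measure that decides Hypothesis 3, and no planned sensitivity analysis would show it.

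The direction follows from the design; the size does not. Under the assumed time values, fares and round trips up to 60 min it runs from HK$0 to about HK$8,000 per fully adherent woman. Travel may be slight for students already on campus, but recruitment also covers a second university and the local community. The documents do not support the stronger statement that the primary cost comparison is biased, because undefined categories could hold part of the cost and time might reasonably be valued at zero. The point does not touch the clinical outcomes or Hypotheses 1 and 2. It should be settled before data collection but is not critical to the trial as a whole.

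**What to change.** In the Economic evaluation section and under Hypothesis 3, add a cost line for participant travel and time for HIAT sessions, in the societal analysis only. Define short-term direct costs and intervention costs so that the two lists agree and nothing is counted twice.

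Ask each woman her usual round-trip time and fare once, at her first session, and take the number of sessions attended from the supervision record. Include fares in the societal total. Report the societal cost difference, ICER and acceptability curve with session and travel time valued over a stated range, from zero to the rate used for absenteeism.

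The cost is two extra questions, one more line in the cost table, and a societal result that may be less favourable to HIAT. Asking at the first session avoids having to rely on recall later.
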